### 10.2 Role of Data Management

#### 10.2.1 *Clinical site responsibilities in data collection and management.*

Local investigators or assigned coordinator are responsible to timely collect the data as required by CRF. Effort should be made to minimize missing data and inaccurate data. All missing data must be explained. If a space on the CRF is left blank because the procedure was not done or the question was not asked, write "N/D". If the item is not applicable to the individual case, write "N/A". If any entry error has been made, to correct such an error, draw a single straight line through the incorrect entry and enter the correct data above it. All such changes must be initialed and dated. DO NOT ERASE OR WHITE OUT ERRORS. They are also responsible to input the collected data into electronic database. The data collected in CRF will be de-identified. Local investigator or coordinator will be responsible to keep the confidential of the data collected.

#### 10.2.2 *DCC responsibilities in data management.*

The data coordinator center (DCC) will conduct monthly comprehensive data checks, as well as regular manual checks (within the database system). Manual checks will identify more complicated and less common errors. The data manager will query sites until each irregularity is resolved. The data coordinator center will also responsible for the database clean-up and final data analysis.

### 10.3 Quality Assurance

Quality control of data will be handled at three different levels. The first level is the real-time logical and range checking built into the web-based data entry system. The research coordinators and data entry clerks at the participating sites are required to ensure the data accuracy as the first defense. The second is the remote data monitoring and validation that is the primary responsibility of the data manager and programmer at the DCC. The data manager will conduct monthly comprehensive data checks, as well as regular manual checks (within the database system). Manual checks will identify more complicated and less common errors. The data manager will query sites until each irregularity is resolved. The third level of quality control will be the site visits, where data in our database will be compared against source documents. Identified errors will be resolved between the DCC and clinical sites. The visits will assure data quality and patient protection.

### 10.4 Adverse Experience Reporting

The site PI will report the SAE by completing and signing the Serious Adverse Event Report Form within 24 hours of discovery, and then emailing document in PDF format to the protocol PI. The site PI must determine and record on the SAE form whether the SAE is unanticipated or anticipated, and if it is related, possibly related, or unrelated to participation in the research. Then the protocol PI will determine whether the SAE need to be reported to DCC or not. If DCC has been reported to, DCC staff will enter the SAE information in the central database and report to DSMB. Upon receiving notification of an SAE, the DSMB will review it via a closed-session email or conference-call discussion. Then DSMB will send a report to DCC within two weeks; reports for life-threatening SAEs will be submitted in one week. The DSMB report will include: statement indicating what related information the DSMB reviewed; the review date; the DSMB's assessment of the information reviewed; and the DSMB's recommendation, if any, for the DCC. The DCC will forward reportable events to protocol PI and all investigators. The Protocol PI will evaluate the frequency and severity of the SAEs and determine if modifications to the protocol and consent form are required. Site PIs will report the SAE to their site IRB according to local IRB requirements.

Responsibilities of PI at Site of SAE:

1. Site PI should determine and sign on the SAE form if the adverse event is: Unanticipated or Anticipated Related, possibly related or unrelated to participation in the research
2. Reporting is done by submitting the SAE form with the PI's signature in PDF format to the Protocol Leader via email.
3. Reporting timeline:
  - i. Unanticipated and related/possibly related SAE must be reported to the protocol PI within 1 business day of discovery.
  - ii. Anticipated and related/possibly related SAE must be reported to the protocol PI within 5 business days of discovery.
  - iii. Unrelated SAE (anticipated or unanticipated) must be reported to the protocol PI within 10 business days (no more than 3 weeks) of discovery.
4. If the SAE is ongoing, the site PI will send follow-up reports to the protocol PI until the SAE is resolved.

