## 5.2 Handling of Study Interventions

Embryo biopsy and NGS will be performed at local sites.

- 1) Embryo biopsy should be completed by the same embryologist at each study site, who has more than 3-years experience to minimize damage on embryos, and different micromanipulators and different laser frequency used in the participating IVF centers are allowed. Biopsy should be performed on Day 5 of embryo culture when blastocysts reach score 4BC or better and fully expand. The biopsy site should be right opposite to the ICM and only 3-5 herniating TE cells will be aspirated. After the operation, survival

03/07/2017

of the embryo is regarded as a success and operation time should be recorded. Patient's name, the medical record number and embryo number should be clearly marked to ensure the consistency.

- 2) Different NGS platforms (*Illumina MiSeq/NextSeq550 or Life Tech PGM/Proton*) applied in different IVF centers are allowed. This reflects current practice where different platforms are used. The resolution value is defined as 4Mb. For laboratory environment and facilities, reagent preparation district, WGA preparation district, library preparation district, product purification district and sequencing district should be separated to prevent contamination and buffering area should be set between the adjacent districts. For laboratory technicians, professional training and technical competence is required. For WGA, first, sample-positive control and negative control are necessary; Second, concentration of products detected using Qubit assay should be no less than 20ng/  $\mu$ l, and those of negative control should be less than 10ng/  $\mu$ l; Third, two technicians are needed to prevent confusion when to transfer samples between tubes. For library preparation, the concentration should be more than 0.5 ng/  $\mu$ l and the volume should be no less than 20  $\mu$ l. For sequencing results, the quality control standard of different platforms should be established and complied with. For example, based on Proton of Life Tech, the loading rate should be more than 60%, polyclone rate no more than 40%, low quality rate no more than 30%, and reads counts of each sample larger than 1M. In the last, all operations should be completed by two technicians together in the lab and auditors should audit the original data and check the sequencing report.

This is an open-label unblinded trial because it is not possible to mask the embryo biopsy.

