#### 9.4 Data Monitoring

We will establish an independent Data and Safety Monitoring Board (DSMB) to review and interpret data generated from the study and to review revisions of the protocol prior to their implementation. Its primary objectives are to ensure the safety of study subjects and the integrity of the research data. The DSMB advises on research design issues, data quality and analysis, and research participant protections for the study. The DSMB will hold regular conference calls in English to review the protocol with respect to ethical and safety standards, monitor the safety of the trials, monitor the integrity of the data with respect to original study design, and provide advice on study conduct. The DSMB will review the progress of the trial, adjudicate adverse events, and decide on any premature closure of the study. The call will be coordinated by the DCC who will provide study updates prior to the call via email.

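### Section 10.4 lets the protocol PI decide which SAEs go on to the DCC and DSMB, and sets two conflicting clocks for site reporting

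*Combined protocol and SAP*

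**What the plan says.** Section 10.4 describes a chain. The site PI's report of an SAE to the protocol PI is described as follows: "completing and signing the Serious Adverse Event Report Form within 24 hours of discovery, and then emailing document in PDF format to the protocol PI". Then comes the discretionary step: "Then the protocol PI will determine whether the SAE need to be reported to DCC or not". What follows is conditional: "If DCC has been reported to, DCC staff will enter the SAE information in the central database and report to DSMB". After it is notified, the DSMB has two weeks to report back to the DCC, or one week for a life-threatening SAE. The protocol PI then weighs SAE frequency and severity and decides whether the protocol and consent form should change.

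Later in 10.4, the list of site PI duties gives a second timetable:

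- **Unanticipated and related or possibly related:** "Unanticipated and related/possibly related SAE must be reported to the protocol PI within 1 business day of discovery".
- **Anticipated and related or possibly related:** 5 business days.
- **Unrelated, anticipated or not:** such an SAE "must be reported to the protocol PI within 10 business days (no more than 3 weeks) of discovery".

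Section 9.4 sets up an independent DSMB and says of it: "Its primary objectives are to ensure the safety of study subjects and the integrity of the research data". Its remit includes adjudicating adverse events and deciding on premature closure. Section 5.2 states: "This is an open-label unblinded trial because it is not possible to mask the embryo biopsy".

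**The concern.** An independent board can protect participants only on the information it receives. Here its route to individual SAEs runs through one investigator, in a trial where allocation is not masked. The plan does not say which events that person must forward, how quickly, or that a decision not to forward must be recorded.

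The definition of an SAE in 7.2 includes pregnancy loss after 20 weeks, neonatal death up to 6 weeks after delivery, and congenital anomaly. The Rationale faults existing trials for incomplete tracking of anomalies and of maternal, fetal and infant complications. A discretionary filter in front of the safety board works against that aim.

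The two clocks are a separate defect. A site can meet one and breach the other with the same report, so compliance cannot be judged. Nor is it clear when the board should expect to hear of an event.

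**Working it through.** **Step 1. Trace the route in 10.4.**

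| Step | Condition | Time limit |
|---|---|---|
| Site PI to protocol PI | every SAE | two limits given (step 3) |
| Protocol PI to DCC | protocol PI's decision, no criterion stated | none |
| DCC to DSMB | only if the DCC was told | none |
| DSMB report to DCC | after notification | 2 weeks; 1 week if life-threatening |

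The DSMB's own clock starts on notification. For an event stopped at the second step it never starts.

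**Step 2. Look for another route that would close the gap.** Section 7.3 has all adverse events, serious or not, recorded in the CRF, and 10.1 has CRF data entered online. Section 9.4 has the DCC send study updates before the regular DSMB calls. Sections 10.2.2 and 10.3 add monthly data checks and site visits. None of these says that the updates list every SAE, that SAE forms are reconciled with the CRF, or that an unforwarded SAE must reach the DSMB. Meanwhile 10.4 makes central entry of the SAE conditional on forwarding.

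**Step 3. Put the two clocks on one scale.** Inputs are the limits in 10.4. Assumptions: a Monday-to-Friday week and no public holidays, with discovery on any day of the week. From a weekday, 5 business days is 7 calendar days and 10 is 14. From a Saturday each is one day shorter, and from a Sunday two days shorter. One business day is 1 calendar day from Monday to Thursday or from Sunday, 2 from Saturday and 3 from Friday. The last column subtracts the 1 day allowed by the 24-hour text.

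| Rule in 10.4 | Limit | Calendar days | Excess over 1 day |
|---|---|---|---|
| Opening sentence | 24 hours | 1 | 0 |
| Unanticipated, related or possibly related | 1 business day | 1 to 3 | 0 to 2 |
| Anticipated, related or possibly related | 5 business days | 5 to 7 | 4 to 6 |
| Unrelated | 10 business days, at most 3 weeks | 12 to 14, cap 3 × 7 = 21 | 11 to 13, cap 20 |

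The tiers depend on expectedness and relatedness, not on outcome. A death or life-threatening event that the site judges unrelated falls in the last row.

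**Step 4. Time until the DSMB's report is due.** Write T = s + a + b + d, where s is site to protocol PI, a is protocol PI to DCC, b is DCC to DSMB, and d is the DSMB's turnaround (14 or 7 days). The plan sets no limit on a or b. If both took no time at all, the latest due dates would be:

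- **24-hour clock:** 1 + 14 = 15 days, or 1 + 7 = 8 if life-threatening.
- **Unrelated tier at 14 days:** 14 + 14 = 28, or 14 + 7 = 21 if life-threatening.
- **Unrelated tier at the cap:** 21 + 14 = 35, or 21 + 7 = 28 if life-threatening.

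Any delay in a or b adds to these, so on paper T has no upper bound.

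**The case against.** The strongest reply is that harms reach the trial by other routes. Adverse events go into the CRF regardless of group or suspected cause (7.3). Obstetric and neonatal records are collected after delivery (6.2.4), with a telephone call at 6 weeks (6.2.5). Pregnancy loss and maternal and neonatal complications are secondary outcomes (9.2.2). None of this depends on the protocol PI's forwarding decision.

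That reply stands against one tempting inference, that selective forwarding would bias the comparison of SAEs between arms. Section 9.5 plans no comparison of forwarded SAEs. The documents give no forwarding rate either, so any illustrative relative risk would only restate the rate assumed. The reply does not show that the DSMB sees every SAE while the trial is running.

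Four further points bound the claim.

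- **Filtering is permitted, not shown.** A reader might infer that the DSMB did receive a filtered record. The text shows only that it could.
- **Knowledge of allocation is inferred.** The trial is open-label, but no section describes the protocol PI's own access to assignments.
- **Causality scales.** Section 7.4 has two levels and 10.4 names three, and a reader might infer that this shifts deadlines. It does not. The tiers separate only related or possibly related from unrelated, which maps onto the two levels in 7.4, where unknown causality counts as possibly related.
- **Other safeguards.** Site PIs report SAEs to their own IRBs, and the IRB may modify or stop the study. Unanticipated related events have a 1-business-day limit, close to 24 hours. These reduce the exposure but do not give the DSMB a complete record.

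The clocks might also be reconciled by applying 24 hours to completing the form and the tiers to sending it. But the opening sentence presents completing and emailing the form as how the SAE is reported, and the later list likewise defines reporting as emailing the signed form. Even on the narrow reading, a completed form for an unrelated SAE could wait up to three weeks.

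**Conclusion.** The point holds as a weakness in safety oversight, and it should be corrected.

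- **Discretion.** Section 10.4 makes central SAE entry and DSMB notification depend on a decision by the protocol PI that has no stated criterion and no time limit. No other section guarantees that the DSMB sees the events not forwarded. Its SAE record could therefore be incomplete or late, which sits badly with its remit in 9.4.
- **Clocks.** The two timetables agree closely only for unanticipated, related or possibly related events. For anticipated related or possibly related events the gap is about 4 to 6 calendar days. For events judged unrelated it is about 11 to 13 days (20 at the cap), whatever the outcome.

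The calendar-day figures assume a Monday-to-Friday week without public holidays. The conclusion about discretion rests on the text alone and needs no numerical assumption. It does not extend to the final analysis of outcomes by arm.

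**What to change.** Amend 10.4 so that sites send every SAE form to the DCC at the same time as to the protocol PI. The DCC should enter every one and pass every one to the DSMB within a stated time. The protocol PI may add comments but may not withhold an event.

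The sponsor should also reconcile the 24-hour text with the list of 1, 5 and 10 business days, so that a single timetable governs site reporting. Which timetable stands is for the sponsor to decide.

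The cost is a short amendment and slightly more forms for the DCC and DSMB to process.

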## 11 HUMAN SUBJECTS

### Institutional Review Board (IRB) Review and Informed Consent

This protocol and the informed consent document and any subsequent modifications will be reviewed and approved by the IRB or ethics committee responsible for oversight of the study. A signed consent form will be obtained from the subject. The consent form will describe the purpose of the study, the procedures to be followed, and the risks and benefits of participation. A copy of the consent form will be given to the subject.

### Subject Confidentiality

All laboratory specimens, evaluation forms, reports, video recordings, and other records that leave the site will be identified only by the Study Identification Number (SID) to maintain subject confidentiality. All records will be kept in a locked file cabinet. All computer entry and networking programs will be done using SIDs only. Clinical information will not be released without written permission of the subject, except as necessary for monitoring by IRB.

### Study Modification/Discontinuation

The study may be modified or discontinued at any time by the IRB, or DSMB as part of their duties to ensure that research subjects are protected.

## 12 PUBLICATION OF RESEARCH FINDINGS

Publication of the results of this trial will be governed by the policies and procedures developed by the Steering Committee. Any presentation, abstract, or manuscript will be made available for review by steering committee prior to submission.

## Supplemental Appendix

Table 1. Comparison among different methods for PGS

| Techniques | Brief overview                                                                                                                                                                             | Strengths                                                                                                                                                                                                                                                                                                                                                              | Drawbacks                                                                                                                                                                                                                                                                                                                                                                                                                                                                                                                                                                                                                                                                                                                                                                                                                        | Current status in clinic                                                                                        |
|------------|--------------------------------------------------------------------------------------------------------------------------------------------------------------------------------------------|------------------------------------------------------------------------------------------------------------------------------------------------------------------------------------------------------------------------------------------------------------------------------------------------------------------------------------------------------------------------|----------------------------------------------------------------------------------------------------------------------------------------------------------------------------------------------------------------------------------------------------------------------------------------------------------------------------------------------------------------------------------------------------------------------------------------------------------------------------------------------------------------------------------------------------------------------------------------------------------------------------------------------------------------------------------------------------------------------------------------------------------------------------------------------------------------------------------|-----------------------------------------------------------------------------------------------------------------|
| FISH       | Fluorescence in situ hybridization is a cytogenetic technique that uses fluorescent probes that bind to only those parts of the chromosome with a high degree of sequence complementarity. | 
 
1. FISH can be used in chromosome analysis of embryos produced by Robertsonian translocation carriers.
 
2. Chromosome-specific centromeric and telomeric probes can be designed to distinguish balanced from unbalanced embryos produced by translocation carriers.
 
3. It is cheap and time saving.
 
 | 
 
1. Difficulties in obtaining the required probes with necessary fluoro-chrome/reporter molecule labeling, split signals/signal overlap, and probe target polymorphisms.
 
2. Limited by the number of fluorescently labelled probes, only aneuploidy for chromosome 13, 15–18, 21, 22, X and Y could be detected. But these chromosomes need to be assessed over multiple rounds of hybridization.
 
3. Poorly predictive of aneuploidy as a result of a high rate of false positives when used on single cells
 
4. Influenced by many factors such as the operator's skill in cell-spreading, the hybridization efficiency and the probe quality.
 
5. Blastomere biopsy at Day 3 cleavage stage embryos does impair the implantation potential.
 
 | 
 
1. It has been replaced by more reliable technologies
 
         |
| aCGH       | Comparative genomic hybridization microarrays involve                                                                                                                                      | 
 
1. It has a better resolution than qPCR.
 
2. It can examine all 24
 
                                                                                                                                                                                                                                           | 
 
1. Time consuming and embryos need to be frozen pending the results of the CGH, with associated compro-
 
                                                                                                                                                                                                                                                                                                                                                                                                                                                                                                                                                                                                                                                                        | 
 
1. Now there are a lot of aCGH platforms available in clinic.
 
 |

|                |                                                                                                                                                                                                                            |                                                                                                                                                                                                                                   |                                                                                                                                                                                                                                                                                                                                                             |                                                                                                                                                                                                                                                                                                                    |
|----------------|----------------------------------------------------------------------------------------------------------------------------------------------------------------------------------------------------------------------------|-----------------------------------------------------------------------------------------------------------------------------------------------------------------------------------------------------------------------------------|-------------------------------------------------------------------------------------------------------------------------------------------------------------------------------------------------------------------------------------------------------------------------------------------------------------------------------------------------------------|--------------------------------------------------------------------------------------------------------------------------------------------------------------------------------------------------------------------------------------------------------------------------------------------------------------------|
|                | differential labeling and mixing of biopsy DNA with control DNA prior to hybridization and interpretation of ratios of red and green (two-color) fluorescence upon completion                                              | chromosomes simultaneously.                                                                                                                                                                                                       | 
mise of embryo quality.
 
 
2. Expensive.
 
3. Rely on the unknown database, lower coverage than NGS.
 
4. Lower sequencing depth than NGS.
 
5. It is not possible to use aCGH for balanced translocation, haploid or polyploid embryo, low-grade mosaicism and single mutations
 
 |                                                                                                                                                                                                                                                                                                                    |
| SNP microarray | Single nucleotide polymorphism microarrays involve hybridization of only biopsy DNA (single color) followed by computational comparison of signal intensities to those obtained on separate control DNA hybridized arrays. | 
 
1. Time saving for fresh embryo transfer
 
2. SNP arrays have the added advantage to identify the parental alleles in the embryo as to exclude uniparental disomy (UPD).
 
 | 
 
1. Expensive.
 
                                                                                                                                                                                                                                                                                             | 
 
1. SNP array is commonly used as a gold standard.
 
2. It can provide genotypic information about single gene disorders, UPD, loss of heterozygosity (LOH), DNA fingerprinting and determination of the parental and cell division origins of aneuploidy.
 
 |
| qPCR           | Quantitative real-time PCR                                                                                                                                                                                                 | 
 
1. It does not require whole genome amplification.
 
2. Much more time saving method from which results are available within 4 h of the biopsy allowing fresh blastocyst
 
 | Not reported.                                                                                                                                                                                                                                                                                                                                               | 
 
1. It has been used for detection of aneuploidy (e.g., trisomy 21) of fetal cells in maternal serum.
 
                                                                                                                                                             |

|     |                                                                                                                                                                                                                                                                  |                                                                                                                                                                                                                                                                                                                                                                              |                                                                                                                                                                                                                                                                                                                          |                                                                             |
|-----|------------------------------------------------------------------------------------------------------------------------------------------------------------------------------------------------------------------------------------------------------------------|------------------------------------------------------------------------------------------------------------------------------------------------------------------------------------------------------------------------------------------------------------------------------------------------------------------------------------------------------------------------------|--------------------------------------------------------------------------------------------------------------------------------------------------------------------------------------------------------------------------------------------------------------------------------------------------------------------------|-----------------------------------------------------------------------------|
|     |                                                                                                                                                                                                                                                                  | transfer after trophectoderm biopsy.                                                                                                                                                                                                                                                                                                                                         |                                                                                                                                                                                                                                                                                                                          |                                                                             |
| NGS | After the whole genome amplification, the material is cut into small DNA fragments (of 100–200 base pairs) and placed on a $2 \times 2$ cm ‘chip’. A sequence of each fragment is then compared to a reference sequence. The results are prepared by a computer. | 
 
1. High coverage rate.
 
2. High sequencing depth.
 
3. NGS can analyze aneuploidy or translocation of all chromosomes and also mutations responsible for any single-gene disease.
 
4. High throughput by parallel analysis of multiple samples in a single sequencing run
 
5. Reduced cost.
 
 | 
 
1. The process is complex.
 
2. Time-consuming
 
3. A lot of de novo mutation will be found, so it needs further consideration in explaining the result to the patient.
 
4. The analysis of the output data needs to base on the known database.
 
 | Currently, NGS is thought to be a future and target technology for PGD/PGS. |

Table 3. List of registered randomized clinical trial regrading PGS

| PI                                    | Clinical trial registration number and link | Status  | Treatment groups                                                                                                                                                                                                                                                                      | Main patient population                                                                                                                                                                                                                                                                                                                     | Sample Size | Primary Outcome                           | Secondary outcomes                                                                               | Live Birth rates | Cumulative live birth rates |
|---------------------------------------|---------------------------------------------|---------|---------------------------------------------------------------------------------------------------------------------------------------------------------------------------------------------------------------------------------------------------------------------------------------|---------------------------------------------------------------------------------------------------------------------------------------------------------------------------------------------------------------------------------------------------------------------------------------------------------------------------------------------|-------------|-------------------------------------------|--------------------------------------------------------------------------------------------------|------------------|-----------------------------|
| Reprogenetics
[name] | NCT01946945                                 | Unknown | Experimental: PGS-Frozen SET
All embryos will be hatched on day 3. Patients will have hatching blastocysts biopsied on day 5/6. Embryos will be vitrified. Patients will have a single hatching euploid blastocyst replaced on a thawed cycle.
Control - Standard ART treatment | Age of 18-42
Inclusion Criteria:
1. All patients medically cleared to do a fresh or frozen embryo transfer.
2. Age up to 42 years

Exclusion Criteria:
1. Microsurgical epididymal sperm aspiration (MESA) and Testicular sperm extraction (TESE) patients
2. At least one partner carrier of a chromosomal or genetic | 240         | Improvement in ongoing implantation rates | Determine specificity and sensitivity rates
Correlation of Mitochondrial DNA and implantation | No               | No                          |

| PI | Clinical trial registration number and link | Status | Treatment groups | Main patient population                                                                                                                                                                                                                                                                                                                                            | Sample Size | Primary Outcome | Secondary outcomes | Live Birth rates | Cumulative live birth rates |
